**Fig. 1 Fig1:**
[figure not shown]
Flowchart of the study

### Protocol amendment

The clinical registration of this trial was 9/15/2022, but in the follow-up protocol design, we identified several problems that needed further refinement and modification. The modified protocol will be more consistent with clinical practice, and the clinical feasibility and significance will be further expanded. In addition, we have completed the amendments of the information in the clinical trial registration platform. The amendments are described below:①In the original registration, we defined the four intraoperative time points for special attention as T_0_-T_3_ and did not specify the method to refer to the baseline rSO_2_ time point. The preoperative baseline rSO_2_ measurement time point is now defined as T_0_, and the four intraoperative time points are changed to T_1_-T_4_ to more clearly and more intuitively define the reference measurement;②In the inclusion criteria listed in the clinical registry, we added "massive intraoperative hemorrhage; intraoperative severe subcutaneous emphysema; operative time < 2.5 h, or > 4 h" as exclusion criteria, which should be an intraoperative contingency to discontinue the trial rather than preoperative screening criteria. In addition, we must clarify several discontinuation conditions in this trial: massive intraoperative hemorrhage; intraoperative severe subcutaneous emphysema; operative time < 2.5 h or > 4 h; CDE; Intraoperative change to open operation; Other events that could threaten the patient's safety;③Regarding the sample size, our calculation method remains unchanged, but the clinically meaningful threshold value of the calculation has been changed from the previous "15%" to a more conservative "10%" and the final sample size was increased from 48 to 76 cases. The specific reasons will be described in the sample size calculation;④Through the pilot trial, we found that the use of postoperative cognitive function assessment methods must be combined with the clinical reality, and the application of the Montreal Cognitive Assessment (MoCA) is challenging. Although the sensitivity of MMSE in detecting mild cognitive impairment is not good enough, it has high clinical practicability. As a secondary outcome measure, we can accept the limitations of the MMSE. Therefore, we will finally choose the MMSE scale as the tool for postoperative cognitive function assessment;⑤The previous description of "Absolute Difference" in the outcome of the main study is not appropriate. We will redefine it as "Absolute Change", that is, the actual increase or decrease between the observed value and the baseline value. The replacement of this term will not affect the rest of the experimental protocol.

### Inclusion and exclusion criteria for the trial

#### Inclusion criteria

ASA status I-III;Age ≥ 65 years;BMI 18–28 kg/m^2^;Preoperative MMSE score ≥ 23 points;Conscious and able to think independently;Planned laparoscopic colorectal cancer surgery, no contraindication to surgery;Nonacute fragile brain function (*History of Cerebral Hemorrhage, Cerebral Infarction, TIA, Cerebrovascular Stenosis, PD, Long-term Headache and Dizziness, and no attack or corresponding clinical symptoms within three months*);Consent to participate in the trial.

#### Exclusion criteria

Patients with intracranial hypertension (*hydrocephalus, brain tumors, brain-occupying lesions, *etc*.*);The forehead has a history of surgery, trauma, lesions, and infection;Patients with a history of severe depression, schizophrenia, and other psychoneurological disorders or who have taken antipsychotic or antidepressant medications;Patients with intense visual and hearing impairments who are unable to communicate appropriately;Patients with a combination of severe underlying diseases other than hypertension, diabetes mellitus, COPD, and underlying conditions related to fragile brain function, as defined in the inclusion criteria (*e.g., acute coronary syndrome, severe cardiac arrhythmias, patients with bitter heart, liver, or renal failure, *etc*.*);Patients with preoperative moderate to severe anemia (*Hb* < *90 g/L*);Patients with a preoperative arterial partial pressure of oxygen < 70 mmHg;Patients undergoing an emergency operation or being converted to an open process due to unforeseen circumstances;Patients already involved in other clinical studies may affect the results of this study.

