### Randomization and blinding

Random numbers generated by SPSS 25.0 software will be placed in sealed opaque envelopes for patient selection. Patients will be divided into Groups H and N based on random numbers at a 1:1 ratio, and they will not be aware of the grouping. The randomization process will be completed by a study administrator who is not involved in this study. Due to the operational uniqueness of PHC, only patients, data collectors, postoperative followers, and technicians testing blood indicators could be blinded, while clinical interventionists could not. Patients who meet the screening criteria will immediately be randomly assigned to the intervention and control groups. PETCO_2_ will be set accordingly to achieve the desired intervention, but the anesthetist will not have a set rSO_2_ target. Data for all trial outcomes will be collected by an independent researcher unaware of the treatment allocation. After data analysis, the sequences will be decoded. Notably, the anesthetist performing the intervention will not be involved in assessing postoperative cognitive function, and in principle, all study participants should be blinded except for those who are implementing the intervention.

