### Measurement of PaCO_2_ and arterial blood gas analysis

Immediately after tracheal intubation, the minute ventilation will be adjusted to achieve PETCO_2_ concentrations of 45–55 mmHg in Group H and 35–40 mmHg in Group N. Due to the presence of alveolar dead space, PETCO_2_ maybe 5 mmHg-10 mmHg lower than PaCO_2_, and thus we will measure PaCO_2_ by performing an arterial blood gas (ABG) analysis and further adjust ventilation to achieve the desired PaCO_2_ target range. In addition, we will set 7.2 as the lowest pH limit for Group H. PaCO_2_ and the PETCO_2_ gradient will be maintained at constant levels as much as possible throughout the procedure. If the concentration of PaCO_2_ must be reassessed, for example, ventilation settings must be adjusted, additional ABG samples will be collected at the discretion of the anesthetist. Finally, at the end of the procedure, ABG samples will be collected to record PaCO2 values accurately and to assess whether PaCO_2_ is maintained within target values.

The Roche Cobas b 123 blood gas analyzer measures pH, PaCO_2_, Na^+^, K^+^, Cl^−^, Ca^+^, erythrocyte pressure (Hct), and metabolites (Glu and Lac) in whole blood using a selective motor technique. The pH, PaCO_2_, Na^+^, K^+^, Cl^−^, and Ca^+^ will be measured using the potentiometric method, erythrocyte pressure will be measured using the conductivity method, and PaO_2_ and metabolites will be measured using the current method. The built-in blood gas analyzer module measures total hemoglobin (tHb), hemoglobin derivatives (O_2_Hb, HHb, COHb, and MetHb), oxygen saturation (SO_2_), and bilirubin (Bili) levels using spectrophotometric methods. Notably, sodium heparin is the only anticoagulant allowed for use in the analysis with the Cobas b 123 system. Other anticoagulants, such as citrate, oxalate, fluoride, and ammonia-containing anticoagulants, exert significant effects on blood pH and other parameters and, therefore, should not be used. In addition, blood used for the analysis must be collected from the blood vessels of eligible persons. Under no circumstances should pressure be applied to the puncture site because the blood will begin to clot prematurely if the blood sample is mixed with tissue fluid, even if the sample collection vessel is adequately heparinized. The specimen should be sent for analysis immediately after collection and, in principle, should be tested within 15 min.

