### Statistical analysis

Data will be analyzed using Statistical Package for Social Science 25.0 software. The Shapiro–Wilk test is used to test the normality of continuous variables, expressed as means and SDs if they are normally distributed and as medians and interquartile ranges if they are non-normally distributed. Baseline, Intraoperative, and postoperative indicators between the intervention and control groups are analyzed by t-tests, Mann–Whitney U test, chi-square test, continuous corrected chi-square test, or Fisher's exact test (Table 3). All primary and secondary outcomes analysis will be based on intention-to-treat (ITT) which means all patients who accept randomization will be included in the final statistical analysis, regardless of whether they received the intended intervention. We will also conduct per-protocol (PP) analysis for primary and secondary outcomes. ITT analysis usually attenuates differences between two groups, and PP analysis exaggerates differences between two groups. We will explore the consistency of ITT and PP analysis results and verify the results' reliability if they are consistent in the end. For the primary outcome, linear regression models will be used to generate unadjusted effect sizes with 95% confidence intervals. Preoperative baseline and intraoperative data are also included in the linear model to generate adjusted effect sizes and 95% confidence intervals. The analysis of repeated measures (rSO_2_, Da-jvO_2_, CERO_2_) will be performed using generalized estimating equations (GEE), with patient code (ID) as the within-subject variable, time as the between-subject variable, and rSO_2_, Da-jvO_2_, and CERO_2_ as the dependent variable. The ACE-R scores of the intervention and control groups will also be analyzed by GEE. What we need to be clear is that we will not adjust for multiple comparisons of secondary outcomes at numerous measurement time points, and we will focus on the separate effects of intervention because these results are exploratory. The incidence of CDE and DNR between the intervention and control group will be analyzed by the chi-square test, continuous corrected chi-square test, or Fisher's exact test. The serum NSE and IL-6 concentrations between the intervention and control groups are analyzed by covariance (ANCOVA) analysis, and the least-squares mean (LSM) difference and 95% CI will be estimated. Postoperative adverse events will be analyzed using the safety analysis set, which refers to patients who received at least one intervention in their group. Postoperative adverse events are categorical data, and the chi-square test, continuous corrected chi-square test, or Fisher's exact test will be used for statistical analysis.

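### Unforeseen conversion to open surgery is still an exclusion criterion, although it can only occur after randomisation and contradicts the discontinuation list and the ITT rule

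*Protocol article*

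**What the plan says.** Five places in the protocol article bear on this point.

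- **Inclusion criteria:** eligibility rests on the intended approach: "Planned laparoscopic colorectal cancer surgery, no contraindication to surgery".
- **Exclusion criteria:** the current list contains "Patients undergoing an emergency operation or being converted to an open process due to unforeseen circumstances".
- **Randomization and blinding, and Measurement of PaCO2 and arterial blood gas analysis:** "Patients who meet the screening criteria will immediately be randomly assigned to the intervention and control groups". The allocated ventilation then begins at intubation: "Immediately after tracheal intubation, the minute ventilation will be adjusted to achieve" the group's end-tidal CO2 range. Those delivering the intervention cannot be blinded.
- **Protocol amendment, item 2:** massive haemorrhage, severe subcutaneous emphysema and operating time had been registered as exclusion criteria. The authors now say of them: "which should be an intraoperative contingency to discontinue the trial rather than preoperative screening criteria". The discontinuation conditions that follow include "operative time < 2.5 h or > 4 h; CDE; Intraoperative change to open operation".
- **Statistical analysis:** for all primary and secondary outcomes, "all patients who accept randomization will be included in the final statistical analysis, regardless of whether they received the intended intervention". A per-protocol analysis is run alongside. Adverse events are analysed in a safety set of patients who received any of their group's intervention.

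**The concern.** An exclusion criterion decides who may enter a trial, so it has to be known before randomisation. Unforeseen conversion is known only during the operation, after the patient has been randomised and the allocated ventilation has started. The amendment recognised this problem for haemorrhage, emphysema and operating time. It added conversion to the discontinuation conditions, but the exclusion list still carries it.

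What is at stake is the randomised comparison. A study team that follows the exclusion list could treat a converted patient as never eligible and take that patient out after allocation, while the allocation is known to the anaesthetist. A team that follows the Statistical analysis section would keep the same patient. Two readers of the protocol could therefore build different analysis sets, both with textual support. This affects the primary endpoint at the end of surgery and the secondary outcomes, including MMSE, ICU admission and 30-day mortality.

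**Working it through.** No figure in the plan is disputed, so the main check sets the sections side by side.

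**Order of events**

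1. Screening, on the planned laparoscopic approach (Inclusion criteria).
2. Randomisation, immediately after screening (Randomization and blinding).
3. Intubation, and the allocated ventilation straight afterwards (Measurement of PaCO2 and arterial blood gas analysis).
4. Pneumoperitoneum and surgery. Unforeseen conversion can happen only here.
5. Suture completion, which is T4, the time of the primary endpoint (Outcomes and data collection).

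Conversion at step 4 comes after steps 2 and 3. T4 is defined by the end of suturing and not by the surgical approach, so a converted patient still has a T4.

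**Status of a converted patient under each section**

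| Section | Status |
|---|---|
| Exclusion criteria | Ineligible |
| Protocol amendment, item 2 | Eligible, then discontinued |
| Statistical analysis (ITT) | Analysed |
| Statistical analysis (safety set) | Analysed, since ventilation began before conversion |

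The first row conflicts with the other three. The conflict does not depend on the amendment section: the exclusion list already contradicts the randomisation timing and the ITT rule. Nor is it a difference between superseded and current text, because the exclusion list is current and the discontinuation conditions are stated as current rules.

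**Size**

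Inputs from Sample size calculations: 68 evaluable patients, 10% loss, final sample 76, two-sided 5% significance, 90% power, difference of 8.

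- Reproducing the plan's final size: 68 / (1 - 0.10) = 75.6, rounded up to 76. This matches.
- Allowance for all losses: 76 - 68 = 8 patients.
- The documents give no conversion rate. At an assumed 5%, 76 x 0.05 = 3.8. At an assumed 15%, 76 x 0.15 = 11.4. That is about 4 to 11 patients.

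For power, the documents state no SD. A two-sample t-test with difference 8 gives 68 patients at SD 10, 56 at SD 9 and 82 at SD 11, so SD 10 is assumed. If converted patients were dropped on top of the 10% loss:

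| Assumed conversion | Evaluable patients | Power |
|---|---|---|
| 5% | 76 x 0.95 x 0.90 = 65.0 | about 89% |
| 10% | 76 x 0.90 x 0.90 = 61.6 | about 87% |
| 15% | 76 x 0.85 x 0.90 = 58.1 | about 85% |

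The loss of power is small to moderate. The larger issue is removing patients for something that happened after allocation.

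**The case against.** The strongest reply is that the analysis is already settled. The ITT sentence covers every randomised patient whatever treatment was received, and the safety set captures anyone ventilated as allocated, which a converted patient has been. The Discussion also requires ITT for discontinued patients. Its examples are haemorrhage, emphysema and shock, but they illustrate an open class of life-threatening events that interfere with rSO2. On this view the conversion clause is a leftover phrase in a single-centre trial whose own team wrote the discontinuation rule.

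Much of that stands. A reader might infer that converted patients will be deleted from the data. No section says so; it would follow only from applying the exclusion list after randomisation. A reader might also infer that safety results would look too favourable. The documents do not support this: it would require both the ITT rule and the safety set to be disregarded, and a difference between arms in conversions or their consequences, for which there is no evidence.

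What does not stand is that nothing needs changing. The ITT rule and the exclusion list are both current and point opposite ways. The Discussion does not name conversion, and not every conversion is life-threatening. Reading the clause as a change of plan before randomisation is strained: it speaks of an unforeseen conversion, and the planned approach is already an inclusion criterion.

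A reader might also see the operating-time limits as the same error. They are not: those limits were moved out of the exclusion list, so there is no matching contradiction. Nothing says measurement stops at discontinuation, and whether the limits should stay is for the investigators.

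**Conclusion.** The contradiction is real and can be seen from the text alone. Unforeseen conversion is an exclusion criterion in one section, a discontinuation event in another, and no bar to analysis in a third. Applied as written, the criterion would be a post-randomisation exclusion made while the allocation is known to the anaesthetist. Confidence in this mismatch is high.

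The consequences are conditional. They arise only if the exclusion list is allowed to override the ITT rule. The number affected rests on an assumed 5-15% conversion rate and the power figures on an assumed SD of 10; neither comes from the documents. No direction of bias can be stated. The point should be corrected because it is a written rule that would damage the randomised comparison if followed, and because the protocol already states the principle that resolves it.

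**What to change.** 1. Delete the part of the exclusion criterion that concerns conversion, leaving the part on emergency operations. The inclusion criterion already covers the planned approach.
2. Treat conversion only as a post-randomisation event, as the Protocol amendment section already does.
3. State that patients who meet any discontinuation condition, including conversion and operating time outside 2.5 to 4 h, stay in the ITT set and, where they received their group's ventilation, in the safety set. T4 rSO2, MMSE, adverse events and 30-day mortality should still be collected for them.
4. State how these patients are handled in the per-protocol analysis, and confine any exclusion to that analysis.

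Which events should stop the trial for a patient, operating time included, is left to the investigators. The sections need only be reconciled so that discontinuation neither ends data collection nor removes a patient from ITT.

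The cost is a few lines of protocol wording and a registry update where the registry carries the clause. Keeping converted patients may slightly widen the spread of T4 values.

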### Randomization and blinding

Random numbers generated by SPSS 25.0 software will be placed in sealed opaque envelopes for patient selection. Patients will be divided into Groups H and N based on random numbers at a 1:1 ratio, and they will not be aware of the grouping. The randomization process will be completed by a study administrator who is not involved in this study. Due to the operational uniqueness of PHC, only patients, data collectors, postoperative followers, and technicians testing blood indicators could be blinded, while clinical interventionists could not. Patients who meet the screening criteria will immediately be randomly assigned to the intervention and control groups. PETCO_2_ will be set accordingly to achieve the desired intervention, but the anesthetist will not have a set rSO_2_ target. Data for all trial outcomes will be collected by an independent researcher unaware of the treatment allocation. After data analysis, the sequences will be decoded. Notably, the anesthetist performing the intervention will not be involved in assessing postoperative cognitive function, and in principle, all study participants should be blinded except for those who are implementing the intervention.

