## Methods

### Study design, setting and participants

Between October 2022 and July 2023, we plan to conduct an RCT at Shengjing Hospital of China Medical University (Shenyang, China), a university teaching, higher education, large general hospital. The trial period is expected to be 10 months, during which patient recruitment, intervention implementation, and postoperative follow-up will be conducted in an orderly manner according to the actual situation. The final results are expected to be reported in October 2023. Participants will be screened from the patients proposed for elective laparoscopic colorectal surgery in the gastrointestinal surgery department of the hospital. Patients who are eligible for elective major surgery are identified after a preoperative evaluation and receipt of written informed consent before the patient's surgery date. Patients who meet the screening criteria will be randomly assigned 1:1 to the control group (Conventional ventilation group parameters: Tidal volume10 ~ 12 mL/kg, Respiratory rate 14 ~ 16 bpm, Suction/Respiration ratio 1:2, PaCO_2_ 35 ~ 45 mmHg, PEEP 0 cmH_2_O, FiO_2_ 40%) and the intervention group (Permissive hypercapnia group parameters: Tidal volume 6 ~ 8 mL/kg, Respiratory rate 12 ~ 14 bpm, Suction/Respiration ratio 1:2, PaCO_2_ 45 ~ 55 mmHg, pH > . 7.2, PEEP 0 cmH_2_O, FiO_2_ 40%), and 38 patients will be included in each group. Baseline preoperative rSO_2_ values will be recorded, and real-time intraoperative rSO_2_ monitoring will be performed by investigators who are not providing the clinical intervention. In addition, patients will be followed up postoperatively with MMSE scale to assess early postoperative cognitive function. The patients with postoperative MMSE scores ≤ 23 and a decrease of more than 2 points from the baseline value were defined as delayed neurocognitive recovery (DNR). It should be noted that the follow-up personnel have received standardized training in advance, to ensure that the survey scale can be used scientifically and correctly (Fig. 1).

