#### Secondary endpoints

Intraoperative T_1_, T_2_, T_3_, and T_4_ cerebral oxygen metabolism-related indexes (*rSO*_*2*_*, Da-jvO*_*2*_*ml/L, CERO*_*2*_*%*);Incidence of CDE (≥ *20% reduction in cerebral oxygen saturation relative to baseline or absolute rSO*_*2*_ ≤ *55%*);MMSE scores 1d before and 1, 3, and 7d after surgery and the incidence of DNR;1d preoperatively (baseline) and 1d postoperatively: serum neuron-specific enolase (NSE) and interleukin-6 (IL-6) levels;Time to awaken from anesthesia;Postoperative admission rate to ICU;The all-cause mortality rate at 30 days postoperatively (*follow-up*);Pulmonary complications after surgery (*bronchospasm, atelectasis, exacerbation of chronic lung disease, infection, prolonged mechanical ventilation, and respiratory failure*);Duration of the hospital stay;Presence of postoperative adverse events (*nausea, vomiting, hypotension, bradycardia, and excessive sedation*): ①A 20% reduction in systolic blood pressure relative to baseline or MAP < 65 mmHg is defined as a perioperative hypotensive event; ②Heart rate < 50 beats/min is defined as bradycardia; ③Level of sedation assessed using the Ramsay scale (*Level 1 awake*: the patient is anxious, restless or irritable; *Level 2 awake*: the patient is cooperative, well-oriented or quiet; *Level 3 awake*: the patient responds only to commands; *Level 4 sleep*: the patient is responsive to tapping between the eyebrows or strong vocal stimuli; *Level 5 sleep*: the patient is unresponsive to tapping between the eyebrows or strong verbal stimuli; *Level 6 sleep*: the patient does not respond to tapping between the eyebrows or strong verbal stimuli), where a Ramsay level ≥ 3 is defined as excessive sedation.

(**T**_**0**_: Immediately after entry, before any treatment **T**_**1**_: 15 min after tracheal intubation **T**_**2**_: 60 min after pneumoperitoneum **T**_**3**_: 120 min after pneumoperitoneum **T**_**4**_: suture completion, end of surgery).

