### Operating method

In this study, we will use a FORE-SIGHT regional oximeter (CAS Medical Systems, Inc.) to collect rSO_2_. This regional oximeter monitors intracerebral rSO_2_ using NIRS and reflectance oximetry, displaying absolute rSO_2_ values and trends. Absolute oximetry values will be defined as rSO_2_ measured with an oximetry probe calibrated with a fixed arterial-to-venous blood ratio. In our study, only absolute oximetry data will be extracted and analyzed. We will install NIRS sensors on each side of the patient's forehead and measure rSO_2_ in both brain hemispheres. Baseline rSO_2_ will be recorded before the start of any medication and before induction of anesthesia, and subsequent rSO_2_ measurements will be recorded every 10 s until the last surgical suture is complete. At the end of the procedure, the data for the entire test cycle will be read via a memory stick through the USB port on the instrument. Moreover, the data collected (within the first two hours of surgery) will finally be presented as a line graph with data visualization software (GraphPad Prism) to visualize the temporal trend of changes in rSO_2_ in both hemispheres. Although we will perform dynamic acquisition of rSO_2_ values throughout the procedure for each patient, the visualization will be limited to 2 h after the start of the procedure due to the substantial variation in the time of the procedure between patients. The absolute change in percent change in rSO_2_ will be calculated by subtracting the baseline rSO_2_ value (T_0_) from the value measured at the end of the procedure (T_4_), multiplied by 100%. The investigators will collect rSO_2_ data from the sensors placed on the patient's left and right forehead.

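### Allocation on passing screening, before the theatre baseline T0, puts patients who are never operated on into the ITT set with no primary outcome: an avoidable but modest loss

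*Protocol article*

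**What the plan says.** All references are to the protocol article.

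- **Screening.** Under Study design, setting and participants, eligible patients are "identified after a preoperative evaluation and receipt of written informed consent before the patient's surgery date". Under Protocol amendment, haemorrhage, emphysema and operating time outside the stated window were taken out of the exclusion list because each is "an intraoperative contingency to discontinue the trial rather than preoperative screening criteria". Screening is therefore a preoperative step.
- **Allocation.** Under Randomization and blinding: "Patients who meet the screening criteria will immediately be randomly assigned to the intervention and control groups". Sealed opaque envelopes are used. Nothing makes allocation wait for arrival in theatre or for a baseline reading.
- **Baseline.** The time-point list under Secondary endpoints defines T0 as "Immediately after entry, before any treatment". Operating method adds that baseline rSO2 "will be recorded before the start of any medication and before induction of anesthesia". Anesthesia induction has the monitors connected after the patient has been brought to the operating room.
- **Primary endpoint.** Operating method defines it as the T4 reading less the T0 reading: "The absolute change in percent change in rSO_2_ will be calculated by subtracting the baseline rSO_2_ value (T_0_) from the value measured". Both readings are needed.
- **When the arms diverge.** Under Measurement of PaCO2 and arterial blood gas analysis: "Immediately after tracheal intubation, the minute ventilation will be adjusted".
- **Analysis set.** Statistical analysis counts everyone who accepts randomisation, whether or not the assigned ventilation was given.
- **Allowance.** Sample size calculations gives 68 patients, raised to 76 for 10% loss.

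**The concern.** The order of events appears to be screening, allocation, then T0. Between allocation and theatre an operation can be called off. Such a patient has been randomised and belongs to the intention-to-treat set, but has neither half of the primary endpoint and was never exposed to either ventilation strategy. No later analysis can recover that information.

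The trial gains nothing from allocating early, because treatment is the same in both arms until after intubation. At stake is a small number of empty randomisations. They draw on the same 8 places that must cover every other cause of a missing primary outcome.

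**Working it through.** **Step 1: order of events.** Set side by side, the sections give: evaluation and consent before the surgery date; allocation at once on meeting the criteria; T0 on entry, before medication and induction; ventilation set by arm after intubation; T4 at suture completion. Allocation before T0 follows from the word for immediacy combined with preoperative screening. It remains an inference, because no time or place for opening the envelope is given and the flowchart (Fig. 1) is not available in the text reviewed.

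**Step 2: who loses the outcome.** The endpoint needs T0 and T4.
- Never operated on: no T0 and no T4, so no outcome.
- Postponed: both readings can be taken at the later operation.
- Changed to open surgery: T0 is on entry and T4 is at the end of surgery. Neither reading requires laparoscopy, so both can exist.

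Only the first group necessarily lacks the outcome.

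**Step 3: the plan's own figures.** Inputs from Sample size calculations: difference 8 points (0 against 8), two-sided 5%, 90% power, unpaired t-test, 68 in total, 10% loss.
- Inflation: 68 / 0.90 = 75.6, rounded up to 76. The stated figure is reproduced.
- Allowance: 76 − 68 = 8 patients.
- The SD is not stated. Solving backwards, 34 per arm results for an SD between about 9.88 and 10.02. SD 9 would give 28 per arm and SD 11 would give 41. SD 10 is assumed below.

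**Step 4: power when some never reach theatre.** The article gives no rate for this, so a range is assumed. The losses are taken in addition to the planned 10%. Evaluable n = 76 × (1 − pre-theatre loss) × 0.90. Power is for a two-sample t-test with standardised difference 8/10 = 0.8. Total needed = 68 / [(1 − pre-theatre loss) × 0.90], rounded up.

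| Never reach theatre (assumed) | Patients of 76 | Evaluable | Power | Total needed |
|---|---|---|---|---|
| 0% | 0 | 68.4 | 90.3% | 76 |
| 3% | 2.3 | 66.3 | 89.4% | 78 |
| 5% | 3.8 | 65.0 | 88.8% | 80 |
| 10% | 7.6 | 61.6 | 87.0% | 84 |

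If the sponsor meant the 10% to cover these patients as well, planned power is unchanged, but at 5% they use 3.8 of the 8 places. With allocation after T0, the pre-theatre loss is close to zero and 76 stands.

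**The case against.** **The timing is inferred.** This is correct. The article does not say that the envelope is opened on the day of screening, and it may in practice be opened in theatre. If so, the text should say so; as written, it points the other way.

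**A reader might infer that T0 itself is biased**, because the anaesthetist who will deliver the arm could know it when the baseline is read. The documents do not support that as a main concern. Study design, setting and participants assigns rSO2 recording to investigators who do not deliver the intervention. Randomization and blinding keeps patients and data collectors unaware of the arm. T0 is a device reading taken before any treatment. No mechanism for a shift by arm is described, so no size can be put on one. The linear model for the primary outcome also includes preoperative baseline data, and Table 3 lists rSO2 among the baseline characteristics.

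**A reader might also infer that every cancelled, postponed or converted case lacks the outcome.** As Step 2 shows, that is too broad.

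**The loss fits within the allowance and is unlikely to differ by arm.** This largely stands. Losses before any arm-specific procedure, in patients who do not know their arm, have no evident route to bias. But the same 8 places must also absorb any T4 readings lost through the discontinuation conditions.

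**Handling of missing outcomes belongs in the analysis plan.** This is accepted, and its absence is not criticised here. The point is that the chosen sequence creates missing outcomes that need not arise.

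**Conclusion.** The point holds as a matter of sequence and efficiency. Read together, the sections place allocation before T0, although the trial does not need the arm to be known until ventilation is set. Patients allocated but never operated on then count in the intention-to-treat set without a primary outcome.

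The size is modest: about 1 point of power at an assumed 5% loss before theatre and about 3 points at 10%, on top of the planned 10% and with an assumed SD of 10. The conclusion rests on the inferred time of envelope opening and on an unknown rate of patients who are never operated on. It is not a finding that the baseline is biased, nor that the intention-to-treat definition contradicts itself. The change is worth making because it costs almost nothing.

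**What to change.** Under Randomization and blinding, replace immediate allocation on passing screening with a statement that the next sealed envelope is opened in theatre once the T0 rSO2 reading is stored and the planned laparoscopic operation is confirmed as going ahead, and before ventilation is set after intubation. If this is already the practice, the sentence only records it.

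Consent, screening, the preoperative MMSE, the interventions and the sample size stay as they are. Envelopes are already in use, so the added work is having the next one at hand in theatre and opening it out of sight of the person recording rSO2. The small downside is that the anaesthetist learns the allocation only shortly before intubation. The change does not prevent losses that arise during surgery, such as conversion or discontinuation; those patients remain randomised and in the intention-to-treat set.
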